## Abstract

**Background:**

Although smartphone-based clinical training to support emergency care training is more affordable than traditional avenues of training, it is still in its infancy and remains poorly implemented. In addition, its current implementations tend to be invariant to the evolving learning needs of the intended users. In resource-limited settings, the use of such platforms coupled with serious-gaming approaches remain largely unexplored and underdeveloped, even though they offer promise in terms of addressing the health workforce skill imbalance and lack of training opportunities associated with the high neonatal mortality rates in these settings.

**Objective:**

This randomized controlled study aims to assess the effectiveness of offering adaptive versus standard feedback through a smartphone-based serious game on health care providers’ knowledge gain on the management of a neonatal medical emergency.

**Methods:**

The study is aimed at health care workers (physicians, nurses, and clinical officers) who provide bedside neonatal care in low-income settings. We will use data captured through an Android smartphone-based serious-game app that will be downloaded to personal phones belonging to the study participants. The intervention will be adaptive feedback provided within the app. The data captured will include the level of feedback provided to participants as they learn to use the mobile app, and performance data from attempts made during the assessment questions on interactive tasks participants perform as they progress through the app on emergency neonatal care delivery. The primary endpoint will be the first two complete rounds of learning within the app, from which the individuals’ “learning gains” and Morris G intervention effect size will be computed. To minimize bias, participants will be assigned to an experimental or a control group by a within-app random generator, and this process will be concealed to both the study participants and the investigators until the primary endpoint is reached.

**Results:**

This project was funded in November 2016. It has been approved by the Central University Research Ethics Committee of the University of Oxford and the Scientific and Ethics Review Unit of the Kenya Medical Research Institute. Recruitment and data collection began from February 2019 and will continue up to July 31, 2019. As of July 18, 2019, we enrolled 541 participants, of whom 238 reached the primary endpoint, with a further 19 qualitative interviews conducted to support evaluation. Full analysis will be conducted once we reach the end of the study recruitment period.

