### Participant Timeline

Enrolment of study participants began on February 1, 2019, and will continue up to July 31, 2019. Because the rollout of LIFE’s intervention in this study is based on the principles and outcomes of an implementation study [36] and informed by self-regulated self-directed learning [37-39], it seeks to understand and work within real-world conditions, rather than trying to control for adoption, acceptability, coverage, and sustainability conditions or remove their influence on the study outcome [36]. Subsequently, to optimally maintain fidelity to LIFE’s planned scale-up, no training sessions are planned for the study participants. Although LIFE is designed for low-income contexts, we set no limit by geographical coverage for self-directed health care providers who might be interested in undertaking this training. However, for primary outcome analysis, participants from high-income countries will be omitted. Participants without any geographic location data (due to refusal to grant the LIFE app the required Android permissions) will be assumed to be from developing countries, given that our recruitment efforts are directed toward professional groups in these countries.

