### Sample Size Calculation

Similar interventions in other subject domains have been found to have an mean effect size of 0.22 (95% CI 0.16-0.27) from a meta-analytic fixed-effects model [24]. To detect an effect size of 0.22 with a two-sided 5% significance level and a power of 80%, a sample size of 83 participants per group, who reach the primary endpoint of the study, is necessary. A sample size calculation for a one-way ANOVA, together with one-sample and paired-sample *t* test analysis using the same effect, power, and significance parameters produce the same required sample size. We anticipate recruiting this number of participants (N=166) in 6 months. The sample size calculation formula is given in the Multimedia Appendix 1.

Based on the alpha and beta tests of the LIFE version, we are assuming a 50% dropout rate of study participants, with drop-out defined as the incomplete or single use of the LIFE smartphone app. We plan to recruit at least 332 participants to account for this dropout rate. To encourage repeated usage of LIFE, participants will receive up to three email reminders from the time they are enrolled into the study, spread over 3 weeks. Demographic data will be collected in the app during its initial use by study participants at the end of the first learning session. Thus, for learners who drop out before completing the first session, or chose not to fill in those data, no demographic data will be available. Logistic regression analyses will be performed on these data to evaluate whether there is a systematic bias caused by attrition of study participants that affects the interaction between the study groups and performance, exposure to previous ETAT+ training, clinical cadre, age of participant, and level of experience. In an effort to ensure participant recruitment is at par with the required study sample size, a monthly target of 30 participants, evaluated at the end of each month, has been set for this study.

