## Results

This project was funded in November 2016. Data were collected from February 2019 up to July 2019. As of July 2019, we enrolled 541 participants, of whom 238 reached the primary endpoint, with a further 19 qualitative interviews conducted to support evaluation (New-Born Unit in-charge nurses, n=4; Paediatric Intensive Care Unit nurses, n=5, final-year medical students already doing clinical rotations, n=4; and student clinical officers and nurses already doing clinical rotations, n=6). Full analysis will be conducted once the number of required participants is met, and the results are expected to be published by Spring of 2020.

Based on the education literature [24,44,45], an effect size of approximately 0.2, 0.5, and 0.8 will be considered small, moderate, and large, respectively. These thresholds represent the magnitude of effect and reflect our assumption that a statistically significant result is not necessarily important or meaningful; for example, for an effect size of 0.2, the difference between the study groups is trivial even if it is statistically significant [44,46].

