## Discussion

This study will be used to explore the effectiveness of adaptive feedback for learning in smartphone-based training for health care workers in a low-income setting. This aspect of medical education is a largely unexplored topic. In this randomized experiment, the risk of performance bias across arms is moderate, given that the active ingredient of the intervention (ie, knowledge) is a latent trait that is difficult to comprehensively control for in a real-world setting. However, the influence of any resulting bias’s ability to alter the results will be assessed within this study using qualitative interviews with study participants.

To help minimize attrition in the study, participants in all study arms who have not reached the primary endpoint will receive up to three email reminders to use the smartphone app from the time they are enrolled into the study, every couple of weeks. The email message will also include a running counter of how many other participants from across the arms of the experiment have successfully played the game so far. The locally accessible study participants will be reimbursed for the mobile data costs incurred when downloading the game if that proves to be a barrier. Whether mobile data charges are a barrier to recruitment of participants and playing the game numerous times will be evaluated through qualitative interviews on an ongoing basis throughout the study period. In case the participant recruitment does not meet the monthly targets, where possible, nonmonetary incentives (such as provision of clinical guidelines protocol booklets) will be phased in to motivate participation in the study.

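### Enrolment and data collection close on the same day, so late enrollees still in progress count as dropouts; the analysis trigger is also stated in two different ways

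*Protocol article*

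**What the plan says.** **Closing dates.** The Abstract (Results) closes recruitment and data collection together: "Recruitment and data collection began from February 2019 and will continue up to July 31, 2019". Participant Timeline keeps enrolment open to the same day: "Enrolment of study participants began on February 1, 2019, and will continue up to July 31, 2019". The main-text Results gives no later end to data capture: "Data were collected from February 2019 up to July 2019". No follow-up after the last enrolment is stated.

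**Endpoint and dropout.** Outcomes defines the primary endpoint as two complete learning rounds, one serving as pretest and the other as posttest. Sample Size Calculation counts a learner as a dropout if use of the app was not completed or happened only once. It sets no minimum time under observation.

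**Reminders.** Sample Size Calculation says that "participants will receive up to three email reminders from the time they are enrolled into the study, spread over 3 weeks". The Discussion spaces the same three emails differently: "from the time they are enrolled into the study, every couple of weeks".

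**Use of dropout.** Sample Size Calculation plans logistic regression to look for systematic bias from attrition. Statistical Methods and Planned Analysis will report dropout numbers and discuss them in terms of self-regulated learning. It also rules out an intention-to-treat analysis, so only learners with two rounds are analysed.

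**Analysis trigger.** The Abstract says "Full analysis will be conducted once we reach the end of the study recruitment period". The main-text Results says "Full analysis will be conducted once the number of required participants is met".

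**The concern.** Learning is self-paced, and the plan's main means of bringing people back for a second round is a set of reminders counted from each enrolment. With enrolment open until the day data collection ends, the last learners to join have little or no time to receive those reminders. Anyone among them still short of a second round at the cut is labelled a dropout, although the calendar stopped their observation.

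Two planned uses of dropout suffer. The logistic regression would treat administrative truncation as attrition. The discussion of dropout as a matter of self-regulation would include people who simply ran out of time. The completer analysis would also miss late enrollees who would have finished a little later.

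Separately, one sentence ties the full analysis to a date and another to a count. The count had been passed in total while recruitment was still open, so the sentences do not describe the same moment. A plan should fix its data cut in one way, particularly as Randomization says blinding does not extend to the analysis stage.

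**Working it through.** **Inputs from the documents**
- Enrolment period: 1 February to 31 July 2019 (Participant Timeline), 181 days counted inclusively.
- Status at 18 July 2019, day 168: 541 enrolled, 238 at the endpoint (Abstract, Results).
- Required completers: 83 per group, 166 in total; planned dropout 50%; recruitment target 332 (Sample Size Calculation). The 83 is taken as stated, since its derivation is a separate matter.

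**Assumptions**
- Accrual is uniform, because no enrolment curve is given.
- The Discussion's reminder spacing is read as two weeks, so three emails span 4 to 6 weeks.

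**1. The plan's own figure.** 166 / (1 − 0.50) = 332, which reproduces the stated target.

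**2. Completion so far.** 238 / 541 = 44.0%, so 56.0% had not reached the endpoint, against 50% planned. That 56.0% already includes people still inside their reminder period on 18 July.

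**3. Projected enrolment.** 541 / 168 = 3.22 per day; 3.22 × 181 ≈ 583 by 31 July.

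**4. Learners with less than the full reminder period.** Share = window / 181; number = 3.22 × window. The last column applies the observed 44.0% and supposes that none of them finishes by the cut.

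| Reminder span | Enrolled after | Share | Learners | Completers forgone, at most |
|---|---|---|---|---|
| 21 days | 10 July | 11.6% | about 68 | about 30 |
| 28 days | 3 July | 15.5% | about 90 | about 40 |
| 42 days | 19 June | 23.2% | about 135 | about 60 |

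**5. Effect on the dropout percentage.** On the same supposition, the inflation is share × completion rate: 11.6% × 44.0% = 5.1 percentage points for 3 weeks, and 23.2% × 44.0% = 10.2 points for 6 weeks.

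**6. How firm the ceiling is.** Each late enrollee who finishes by 31 July lowers these figures. In the other direction, 44.0% may understate eventual completion, because some of the 541 were recent. At the planned 50%, the 3-week figure would be 68 × 0.50 = 34.

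**7. The two triggers.** On 18 July, 238 exceeded 166 and 541 exceeded 332, so the count was met in total while the end of recruitment was still 13 days away. The split by arm is not given. Under coin-toss allocation the expectation is 119 per arm with SD √(238 × 0.25) = 7.7, so an arm of 83 would lie (119 − 83) / 7.7 = 4.7 SD below it. Participant Timeline omits learners in high-income countries; more than 238 − 166 = 72 completers would have to be removed to bring the total below the requirement.

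**The case against.** The strongest reply is that this is mostly a matter of tidying wording. Much of it stands:

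- A reader might infer that everyone enrolled in July is a dropout. That is not so. On the 3-week schedule, people enrolled up to 10 July have the full period, and anyone who finishes two rounds by the cut is a completer whenever they joined.
- A reader might infer that usable data are thrown away. A learner without a posttest at the cut has nothing to analyse, so what is lost is possible future completers.
- A reader might infer a biased treatment effect. Allocation happens at first launch by a coin-toss procedure, so the calendar cut should affect both arms similarly. The documents show no difference between arms arising from it.
- A reader might take the two triggers as defining different data sets, or as a rule to stop when results suit. Both sentences say when the analysis takes place. Neither says that data are cut at the 166th completer, and no interim look is described.
- Accrual was probably uneven: Study Setting and Recruitment describes promotion every couple of weeks and groups convened monthly. No time-to-completion data are given.
- The reminders are an aid to retention, and the protocol does not call them an observation window.

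These points limit the consequence but do not remove the problem. The common closing date is stated outright, dropout has no minimum observation time, and the dropout variable feeds a planned regression and a planned interpretation. The two pairs of sentences still disagree.

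**Conclusion.** The point holds in a limited form. Late enrollees still in progress on 31 July 2019 are counted as attrition without having had the full reminder period. Under uniform accrual, those exposed to this are about 12% of a projected 583 enrollees on the 3-week schedule and about 15% to 23% on a 4- to 6-week reading. Only those unfinished at the cut are affected.

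The consequences are an overstated dropout figure (by at most about 5 percentage points on the 3-week reading, at the observed completion rate), an attrition model that confuses truncation with real attrition, and some possible completers forgone. Bias in the comparison between arms is not shown and should not be claimed.

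The analysis triggers in the Abstract and the main-text Results differ in timing, and the reminder schedules in Sample Size Calculation and the Discussion differ in spacing. Each pair must be reconciled. The change is worth making because it is cheap, but it does not put the primary comparison in doubt.

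**What to change.** 1. State one reminder schedule and use it in both Sample Size Calculation and the Discussion.
2. Close enrolment on 31 July 2019, but keep data capture open until the last enrollee has had the full reminder period: 31 July + 21 days = 21 August 2019 on the 3-week schedule, or 31 July + 42 days = 11 September 2019 at the longest reading.
3. Run one analysis after that date on all eligible learners with two complete rounds, and delete the count-based trigger from the main-text Results.
4. If capture cannot be extended, report learners with less than the full reminder period separately from dropouts and leave them out of the attrition model.

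The primary endpoint should not be restricted to a fixed number of days from first launch. That could remove learners who returned later, from February onwards, and would truncate the time between rounds, which is a planned secondary outcome. Observation time will still differ by enrolment date; the change only guarantees everyone a minimum.

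The cost is a few weeks' delay before data lock. Data Management describes app data being synchronized to an online server, so the longer capture needs little extra work.

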**Conclusions:**

This study will be used to explore the effectiveness of adaptive feedback in a smartphone-based serious game on health care providers in a low-income setting. This aspect of medical education is a largely unexplored topic in this context. In this randomized experiment, the risk of performance bias across arms is moderate, given that the active ingredient of the intervention (ie, knowledge) is a latent trait that is difficult to comprehensively control for in a real-world setting. However, the influence of any resulting bias that has the ability to alter the results will be assessed using alternative methods such as qualitative interviews.

**Trial Registration:**

Pan African Clinical Trials Registry PACTR201901783811130; https://pactr.samrc.ac.za/TrialDisplay. aspx?TrialID=5836

**International Registered Report Identifier (IRRID):**

PRR1-10.2196/13034

## Introduction

### Background

In low-income contexts such as Sub-Saharan Africa, the need for health workers to provide care for themselves is more frequent than that in middle- and high-income settings and can be associated with negative neonatal outcomes [1]. Of the estimated 2.9 million neonatal lives (from birth through day 28) lost each year globally, Sub-Saharan Africa has the highest overall risk of death within the first 24 hours of life and accounts for 37% of the global neonatal deaths [1]. This is compounded by severe workforce shortage, coupled with the health workforce skill imbalance and maldistribution, and a lack of training opportunities [2,3]. Additional training is needed to better prepare health providers in these facilities to provide effective emergency pediatric and neonatal care [4,5]; however, unfortunately, face-to-face training costs between US $80 to $300 per person per day and is difficult to deliver at scale [6]. A face-to-face course developed in Kenya (Emergency Triage, Assessment and Treatment plus admission care [ETAT+]) [7,8] has been successfully used to provide training in Kenya as well as eight other low-income countries [9]. ETAT+ has already been used to train over 5000 health care workers and 2000 medical students across Kenya, Uganda, Rwanda, Zimbabwe, Zambia, Malawi, Tanzania, Sierra Leone, and Myanmar. It is part of the undergraduate medical training curriculum in medical schools in East Africa [10]. The aim of the ETAT+ is to familiarize health workers with clinical guidelines and the necessary knowledge and skills for triaging all sick children when they arrive at a health facility into emergency cases with priority signs or nonurgent cases and to provide emergency treatment for those with life-threatening conditions [11]. Only a small fraction of trained health providers have received the basic requisite skills training for newborn resuscitation in this context [12,13]. New strategies are therefore required to improve access for over 1 million health providers across Africa, and training approaches need to be updated efficiently as guidelines change and be able to capture data on how many health workers are trained [14,15].

There is little evidence to support the implementation of learning interventions that are relevant to the context of low-income settings, which takes into account health workers’ initial and continuing clinical training needs and adapts learning content in light of skill mastery and performance as they continue to develop knowledge through it [15-18]. Within low-resource contexts, investigation of learner models (ie, a cognitive model that tries to model observed student learning behaviors) needed to support tailored instruction based on predicted learner’s skill mastery in clinical settings is required [19], as adaptive instructional support has been shown to significantly outperform teacher-led large-group instruction, nonadaptive computer-based instruction, and paper-based instruction in producing learning gains in high-resource settings outside clinical care [19].

Several health care training apps have been developed to date, and the approaches used therein can broadly be divided into two categories. Some replicate existing teaching strategies “on a screen,” for example, by providing questions and answers for exam practice or displaying of textbook graphics. Others take advantage of features specific to mobile devices, examples of which include the ability to respond to user choices with different pathways or the use of animations with which the user can interact [15]. Serious games, which are digital games with a specific, applied purpose (other than entertainment) that can be played on mobile phones, are one such way of providing training with the potential to affect health outcomes [20]. The rationale for using serious games is that, similar to “first-person” computer games, emergency care training should enable health workers to follow highly structured pathways (such as clinical care algorithms) with pieces of information (cues) sought at each step, which determine the correct actions to perform. With both clinical training and performance in computer games, executing cue-response sequences perfectly, rapidly, and automatically demonstrates mastery. This type of mastery has been shown to support effective clinical care delivery, but the required frequency of rehearsal in this approach is difficult and expensive to maintain for face-to-face training [21]. By using a serious gaming approach, users may be more motivated to repeatedly play the serious game, using incentives such as rewards, increasing difficulty, and scores—techniques that have been successfully used to encourage repeated gameplay in nonserious computer games. There is a scarcity of evidence from studies evaluating and assessing serious gaming approaches using smartphones in health care training in low-income settings, but this topic was recently highlighted in the most recent systematic review [22,23].

Efforts to implement innovative educational interventions, which increase the number of well-trained health providers, are yet to capitalize on digital learning approaches that model learners’ knowledge states to provide individualized instruction and have been shown to have considerable positive effects on learning outcomes in other subject areas [5,24,25]. The Life-Saving Instruction for Emergencies (LIFE) project is developing an approach to create serious games for low-cost smartphones initially to provide training for care of very sick newborns and children. The game evolves the scenario-based teaching model that is used in the traditional face-to-face ETAT+ course already described.

The potential for utilizing the digital and reusable nature of interventions such as LIFE, to personalize the way health workers learn and receive feedback on their performance on which they can base future learning, achieve learning objectives, and develop their skills is still underexplored and unknown [18,22]. Additionally, the use of smartphones as experimental tools offers access to a wider pool of study participants due to their ubiquitous nature [26]; can minimize the cost of implementing, evaluating, and scaling an educational intervention such as LIFE in a resource-constrained context [15], and has been shown to raise learners’ interest in knowledge interventions [27].

